## Background

Preterm birth (PTB), defined as birth before 37 weeks of gestation, is in quantity and in severity one of the most important issue in obstetric care in the world. Globally, around 15 million preterm births are born every year [1]. In 2014 the United States it was 9.5% in 2014, while in Brazil, according to the national registry of living births system (SINASC), PTB rate was 9.9% in 2012 [2, 3]. The recent WHO report Born too Soon estimates the number of preterm births in Brazil to be 279,300 (9.1% of live births) [1]. Its prevalence has increased by 30% in the last 30 years and Brazil features among the top-10 countries with the highest numbers of preterm births [4]. Some data suggest that the real prevalence of preterm birth in Brazil approaches 10% [5].

Being born premature increases the risk of death by other causes as infections and is associated with lifelong sequelae such as cerebral palsy, visual deficiency and lower school performance [6]. Prematurity is the major cause of neonatal deaths worldwide and the second most important cause in children under 5 years, after pneumonia. Only in 2010 prematurity was responsible for 35% of 3.1 million neonatal deaths [4].

PTB is a multifactorial condition. The increase in maternal age at conception, multiple pregnancies, and maternal and neonatal related conditions are some of these factors that lead to therapeutic and spontaneous preterm labor. Women with previous PTB, preterm premature rupture of membranes (PPROM), and preterm labor also have a higher risk of PTB [7]. Even knowing some of the causes, almost 50% of the spontaneous PTB have no identifiable cause [7] and a significant reduction of PTB rates has not been accomplished so far.

One raising strategy to reduce PTB is to pay attention to physiological modifications that precede preterm labor in the uterine cervix: the cervical length shortening [8]. There is an inverse relationship between mid-trimester cervical length and the risk of preterm birth that varies as a function of the gestational age at the time the cervical shortening is diagnosed [6].

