### Randomization

After written informed consent, women will be randomized into two groups: the use of pessary plus progesterone or the use of progesterone alone. Randomization will be stratified by center, number of fetuses (one or two) and cervical length (< 25 mm or 25-30 mm) using a 1:1 ratio and variable block sizes. Randomization is performed electronically in an online database added as a specific form in the online data collection system, using computer-generated random numbers. The system can be accessed 24/7 and a phone number is available to help the inclusion and randomization process. Each local coordinator will be responsible for the randomization process including enrollment and assignment of women to interventions.

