### Data analysis

Data analysis will be performed according to the intention-to-treat principle. A statistical analysis plan will be finalized prior to the data lock.

Categorical variables will be expressed by the relative frequency on the corresponding allocation arm. For continuous variables minimum, first quartile, median, third quartile, maximum, mean, and standard deviation will be presented. Missing values will be reported for all variables.

The primary outcome is a binomial random variable. For this outcome, we will estimate a risk ratio (RR) with 95% CI. We will also calculate rates in the two groups as well as the number needed to treat (NNT). The comparisons of treatments will be performed with a generalized linear model [42], with the log link function. The model will include treatment as main effect and a full factorial of study center, type of pregnancy (twin or singleton) and cervix length (two categories). The main analysis will be performed using stratums according the randomization process. All factors are fixed. The factors study center, type of pregnancy and cervix length figure as randomization block terms.

An additional model including cervical length as continuous covariate will also be analyzed. The model better adjusted will be used as final model. The Akaike Information Criterion (AIc) e Bayesian Information Criterion (BIC) will be used to decide among models. To evaluate the potential efficacy of the pessary, a per-protocol analysis will also be performed.

Secondary outcomes will be analyzed using generalized linear models with treatment as main effect and a full factorial of study center, type of pregnancy (twin or singleton) and cervix length (two categories). All factors are fixed. An appropriated link function will be chosen to each response variable.

An additional model including cervical length as continuous covariate will also be analyzed. The model better adjusted will be used as final model. The Akaike Information Criterion (AIc) e Bayesian Information Criterion (BIC) will be used to decide among models.

Survival analysis to assess time to delivery will also be performed using Kaplan Meier and Cox Proportional Hazard Model. Differences in treatments among subgroups will be assessed including in the statistical models already described above a subgroup variable and a interaction term subgroup-treatment. These are the subgroups to be analyzed:

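### The treatment-effect models adjust only for the randomisation strata and omit two recorded predictors of preterm birth, a modest and avoidable loss of precision

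*Protocol article*

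**What the plan says.** All references are to the protocol article.

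- **Primary model (Data analysis).** The effect measure is a risk ratio: "The comparisons of treatments will be performed with a generalized linear model [42], with the log link function". The covariates are fixed: "The model will include treatment as main effect and a full factorial of study center, type of pregnancy (twin or singleton) and cervix length", the last of these dichotomised.
- **Secondary models (Data analysis).** The same set is carried over: "Secondary outcomes will be analyzed using generalized linear models with treatment as main effect and a full factorial of study center, type of pregnancy" and cervical length.
- **Only alternative covariate (Data analysis).** "An additional model including cervical length as continuous covariate will also be analyzed". Cervical length is itself a stratification factor.
- **Strata (Randomization).** "Randomization will be stratified by center, number of fetuses (one or two) and cervical length (< 25 mm or 25-30 mm) using a 1:1 ratio". Obstetric history and gestational age are not strata.
- **Risk factors (Background).** "Women with previous PTB, preterm premature rupture of membranes (PPROM), and preterm labor also have a higher risk of PTB". The relation between mid-trimester cervical length and preterm birth "varies as a function of the gestational age at the time the cervical shortening is diagnosed".
- **Availability at baseline.** Gestational age decides eligibility, in a window from 18+0 to 22+6 weeks (Inclusion and exclusion criteria). Previous spontaneous preterm birth and parity are listed subgroups (Data analysis).
- **Subgroup models (Data analysis).** Subgroup differences are assessed by "including in the statistical models already described above a subgroup variable and a interaction term subgroup-treatment".

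No reason is given for leaving the two variables out of the treatment-effect models.

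**The concern.** A baseline variable that predicts the outcome and is not in the model leaves its variation in the error. The interval for the risk ratio is then wider than the collected data require. A chance difference between arms in that variable also passes into the realised estimate. Here the protocol itself supplies the reason to expect prognostic value, the data are already collected, and the covariate list is fixed in the protocol rather than left open. The planned models treat a given cervical length at 18+0 weeks and at 22+6 weeks as the same risk, although the Background says the relation changes with gestational age.

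The comparison with least room is the subgroup with cervical length of 25 mm or less. It drives the sample size and is planned at about 80% power.

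**Working it through.** **1. Reproduce the planned sizes (Sample size section).** Inputs: two-sided alpha 0.05, power 80%, 22% versus 12%; in the subgroup 17.3% versus 8.65%. Stated: 219 per group and 234 per arm.

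n per arm = [1.960 × √(2p̄(1−p̄)) + 0.842 × √(p₁(1−p₁) + p₂(1−p₂))]² / (p₁−p₂)²

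- Overall: p̄ = 0.17; (1.0412 + 0.4431)² / 0.01 = 220.3, so 221.
- Subgroup: p̄ = 0.12975; (0.9314 + 0.3966)² / 0.007482 = 235.7, so 236.

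Unpooled variance gives 218 and 233. The stated sizes reproduce, with no covariate gain and no dropout allowance built in.

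**2. Power as planned, by the same formula.**

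- 22% versus 12% at 219 per group: 79.8%; at the final 468 per group: 98.3%.
- Subgroup at 234 per arm: 79.7%.

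**3. Variance without the covariates, 468 per arm.**

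Var(log RR) = 0.78/(468 × 0.22) + 0.88/(468 × 0.12) = 0.00758 + 0.01567 = 0.02325; SE 0.1525.

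**4. Variance with the covariates.** The documents give neither prevalence nor effect size, so these are assumptions: previous preterm birth in 10 to 30%, risk ratio 1.5 to 3 for the composite, and risk ratio 1.0 to 1.2 per week of earlier scan over five weeks. The adjusted variance is the treatment entry of the inverse expected information of a log-binomial model, with weights nμ/(1−μ). Strata terms are left out of both sides of the comparison.

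| Assumed (prevalence; RR history; RR per week) | Variance ratio | SE | CI narrower by | Power, 219 per group | Power, 468 per group | Power, subgroup 234 per arm |
|---|---|---|---|---|---|---|
| none | 1 | 0.1525 | – | 79.8% | 98.3% | 79.7% |
| 10%; 1.5; 1.0 | 0.9952 | 0.1521 | 0.2% | 80.0% | 98.4% | 79.9% |
| 20%; 2; 1.1 (middle) | 0.9687 | 0.1501 | 1.6% | 81.0% | 98.6% | 81.0% |
| 20%; 3; 1.2 (top) | 0.8915 | 0.1440 | 5.6% | 84.1% | 99.1% | 84.1% |

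The CI change is 1 − √ratio, on the log scale. Power uses n/ratio per arm. The middle case is worth 936 × (1 − 0.9687) ≈ 29 women. Most of the gain comes from history: with 20% and RR 2, the ratio is already 0.9740 with no gestational-age effect.

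The subgroup column carries over the overall ratio, which is generous because events are rarer there. Recomputed at 17.3% versus 8.65%, the middle case gives a ratio of about 0.979. Then 234/0.979 ≈ 239 per arm, and power is about 80.5%.

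**5. Check by simulation.** 936 women, control risk 22%, RR 0.67, 12% twins, 40% in the shorter stratum, 15% with previous spontaneous preterm birth, robust Poisson, 4000 trials per scenario (all inputs except 936 and 22% assumed):

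| Odds ratio: history; per week of gestation | SD of log RR without → with | Variance reduction |
|---|---|---|
| 2; 0.85 | 0.1422 → 0.1413 | 1.3% |
| 2.5; 0.80 | 0.1412 → 0.1394 | 2.6% |
| 3.5; 0.75 | 0.1424 → 0.1391 | 4.5% |

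By 936 × (1/(1 − reduction) − 1), these equal about 12, 25 and 44 women. A second run under the same assumptions gave 1.6 to 4.7%.

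**6. Chance imbalance.** At 15% prevalence, the SD of the between-arm difference in history is √(2 × 0.15 × 0.85/468) = 2.3 points overall and √(2 × 0.15 × 0.85/234) = 3.3 points in the subgroup. If history doubles risk, a 2-SD imbalance in the subgroup (18.3% versus 11.7%) moves the unadjusted RR by 1.183/1.117 = 1.059, about 6%.

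**7. Room in the model.** The full factorial has 17 × 2 × 2 = 68 cells: 936/68 ≈ 14 women and, at 17% average risk, 159/68 ≈ 2.3 events per cell. Main-effect strata need 1 + 16 + 1 + 1 = 19 parameters including the intercept.

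**The case against.** The strongest reply is that nothing here is an error. Adjusting for the randomisation strata is standard and valid, the estimate is unbiased, and the sample size assumes no covariate gain. All of that stands, and it limits the point to efficiency.

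Other replies also stand in part:

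- The Background speaks of preterm birth, while the primary outcome is a neonatal composite. The prognostic link is therefore indirect for the primary outcome and closer for the secondary preterm-birth outcomes. It also says previous preterm birth without the word spontaneous.
- Gestational age is described as changing the cervical-length relation, so a linear main effect captures only part of that statement.
- The gain is not entirely free. Extra terms on a log-link model with 68 sparse cells could worsen convergence, and that sparsity threatens stable estimation more than the omitted covariates do. The simulation used robust Poisson and is not shown to have fitted the full factorial.
- Randomisation and the confidence interval already allow for chance imbalance.

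A reader might infer that the two variables enter no model at all. The documents do not support that: previous spontaneous preterm birth is a listed subgroup, and the subgroup models add "including in the statistical models already described above a subgroup variable and a interaction term subgroup-treatment" to those already described. A reader might also take from the simulation that overall power rises from about 82% to 83–84%. That rests on RR 0.67, which the protocol does not use; 22% to 12% is RR 0.545, where power is already about 98%.

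**Conclusion.** The point holds as a modest, avoidable loss of precision in the primary and secondary treatment-effect models. The protocol fixes those models on the strata alone, while its own Background and its recorded baseline data point to two further predictors.

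The size is about 1 to 5% of the variance of log RR under the simulation's assumptions, and 0.5 to 11% over the wider range. The top of that range needs a risk ratio of 3 for history together with a strong gestational-age gradient. Overall power at 22% versus 12% changes by less than one point. Power in the 234-per-arm subgroup changes by about one point (0.2 to 4.4, on the generous side for the reason in step 4). None of the prognostic inputs comes from the documents.

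It would be wrong to conclude that the planned estimate is biased or that the trial is underpowered for want of these covariates. The stated sizes reproduce without them.

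**What to change.** In the Data analysis section, and in the analysis plan due before data lock:

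- Add two pre-specified main-effect covariates to the primary model and the secondary generalised linear models: obstetric history (nulliparous; parous without previous spontaneous preterm birth; parous with it) and gestational age at the screening scan, in weeks, linear.
- In the same change, enter centre, type of pregnancy and cervical length as main effects instead of the full factorial. With treatment and the new covariates the model then has 19 + 1 + 3 = 23 parameters, against 68 + 1 = 69 in the planned one.
- Keep the strata-only model as a sensitivity analysis.
- State how missing obstetric history is handled.

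The cost is a few sentences and three more covariate parameters. No new data item is needed.

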### Interventions

Since the use of the pessary cannot be blinded, this is an open-label RCT. The pessary used is an Arabin type pessary registered at the national health surveillance agency of Brazil (Pessário AM® by Ingamed) with the dimensions: inner circle 30 mm; outer circle 70 mm; height 25 mm.

A physician trained specifically for pessary placement will insert the pessary up to 72 h from the randomization. An ultrasound scan to re-assess cervical length and pessary placement will be performed after its insertion.

We will use 200 mg micronized progesterone capsules that will be self-administered digitally inserted into the vagina every night. Commercial Progesterone (Utrogestam®) pills will be purchased from Besins Healthcare Pharmaceutics. Both interventions will be maintained until 36 weeks gestation unless antenatal care providers consider the need to withdrawal earlier.

The intervention will be discontinued before 36 weeks only if the assistant medical doctor judges it is necessary due to clinical conditions, or in case of woman request. Every enrolled woman will receive access to a P5 phone number for her to call in case of doubts or need to report side events. A research assistant will be full time available for solving such questions.

Women with threatened preterm labor will be treated with tocolysis, corticosteroids and magnesium sulfate according to local protocols.

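### AIC/BIC on the observed outcomes picks the final model, so the declared main analysis does not fix the primary risk ratio in advance

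*Protocol article*

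**What the plan says.** All of this is in the Protocol article, Methods, Data analysis.

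- **Effect measure.** "For this outcome, we will estimate a risk ratio (RR) with 95% CI". The model is a generalized linear model with log link.
- **Declared model.** It contains treatment and the full factorial of centre, singleton or twin pregnancy, and cervical length in two categories. The section adds: "The main analysis will be performed using stratums according the randomization process".
- **Competing model.** "An additional model including cervical length as continuous covariate will also be analyzed". Whether the continuous term joins the two-category factor or takes its place is not stated.
- **Choice between them.** "The model better adjusted will be used as final model", and "The Akaike Information Criterion (AIc) e Bayesian Information Criterion (BIC) will be used to decide among models". No order of precedence between the two criteria is given.
- **Secondary outcomes.** The same additional model and the same selection rule are repeated.
- **Timing.** "A statistical analysis plan will be finalized prior to the data lock". That plan is not at hand.

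**The concern.** One sentence identifies a main analysis. The following paragraph hands the role of final model to whichever of two models fits the observed outcomes better. The section does not say how main analysis and final model relate, so a reader cannot tell which risk ratio answers the primary question.

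This is a stated rule, not a detail left open for the statistical analysis plan. Finalising that plan before data lock does not cure it if the rule is kept, because AIC and BIC can be computed only once the outcomes are fitted. The Interventions section says "Since the use of the pessary cannot be blinded, this is an open-label RCT", which is a further reason to have the primary estimate settled beforehand.

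Three consequences follow:

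- Different secondary outcomes may end with different covariate adjustment.
- The data safety and monitoring board is to look at statistical significance for the main outcome after half and after two thirds of randomised cases. Read literally, the selected model could change between those looks and the final analysis.
- If AIC and BIC point to different models, the text gives no answer.

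**Working it through.** **Inputs.** N = 936 women, with 22% versus 12% for the primary outcome (Sample size); 17 centres (Governance); strata of centre, one or two fetuses, and two cervical-length categories (Randomization). I take n in the BIC penalty as the number of women.

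**The plan's own figure.** For 22% versus 12%, two-sided alpha 0.05 and 80% power, the unpooled formula gives (1.960 + 0.842)² × (0.22×0.78 + 0.12×0.88) / 0.10² = 217.6, so 218 per group. The pooled formula gives 221. The stated 219 lies between them and is reproduced. The point does not depend on it; only N = 936 is used below.

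**Penalties.** AIC charges 2 per parameter. BIC charges ln(936) = 6.84. The criteria can disagree only if the two models differ in number of parameters, and that depends on the unstated form of the continuous model.

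1. *Continuous length added as one term (+1 parameter).* AIC takes the larger model if the likelihood-ratio statistic exceeds 2, BIC if it exceeds 6.84. They disagree between those values.
   - No residual effect: P(2 < χ²₁ < 6.84) = 14.8%.
   - Non-centrality 2, 4, 6, 8 (assumed values): 38.8%, 45.2%, 41.6%, 33.7%.
2. *Continuous length replaces the category additively, centre × pregnancy type kept.* The declared model has 17 × 2 × 2 + 1 = 69 parameters and the competitor 17 × 2 + 1 + 1 = 36. The difference is 33, and the penalty gap is 33 × 2 = 66 (AIC) or 33 × 6.84 = 226 (BIC).
3. *Continuous length replaces the category one-for-one inside the factorial.* Parameter counts are equal, so the criteria always agree. The choice still depends on the outcomes.

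**Interim looks.** The BIC charge moves with n: ln(468) = 6.15 at half, ln(624) = 6.44 at two thirds, 6.84 at the end. The same rule therefore has different thresholds at each look.

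**Effect on inference.** The rule was simulated with N = 936: 2,000 trials with no treatment effect and 1,000 with RR 0.7. Assumptions not in the documents: 20% twins, cervical length uniform on 6 to 30 mm, log-risk slope −0.03 per mm, no centre effects, logistic likelihood for AIC and BIC, robust Poisson for the risk ratio.

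| Quantity | Length added (form 1) | Additive replacement (form 2, without centre) |
|---|---|---|
| AIC and BIC disagree, RR 1 / RR 0.7 | 37.7% / 44.1% | 5.6% / 7.4% |
| Type I error, fixed stratified model | 4.3% | 4.3% |
| Type I error after selection by AIC / BIC | 4.2% / 4.35% | 4.15% / 4.15% |
| Type I error if the smaller p-value is taken | 4.55% | 4.5% |
| Models differ on significance, RR 1 / RR 0.7 | 0.6% / 2.0% | 0.55% / 1.9% |
| Power at RR 0.7, fixed model | 77.9% | 77.9% |
| Power at RR 0.7 after selection by AIC / BIC | 78.2% / 77.9% | 78.4% / 78.3% |

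The Monte Carlo standard error of a 4.3% rate in 2,000 trials is √(0.043 × 0.957 / 2000) = 0.45 percentage points, so the type I error rates cannot be told apart.

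**The case against.** The strongest defence is that this is a pre-stated algorithm over two named models, both containing the treatment term. AIC and BIC compare overall fit and do not select on the treatment p-value. That stands. A reader might infer that the rule inflates the false-positive rate or lets the investigators pick the better p-value. The documents do not support that, and the simulation shows no material inflation even when the smaller p-value is taken deliberately. It is also true in principle that the reported interval ignores the selection step, but no harm from this has been shown.

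A second defence is that, if continuous length is added, both candidates keep the randomisation strata, so the sentence about strata stays true whichever model wins. This softens the conflict but does not remove it. The reported model would still not be the one declared, and the text does not say that the term is added.

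A third is that a tie-break between criteria is commonly left to the statistical analysis plan, and that under one form the criteria cannot disagree. Both are fair. The missing tie-break alone would be a weak point.

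A reader might also infer from the 33-parameter gap that the declared model would almost never be chosen. P(χ²₃₃ > 66) is about 0.0006, but that calculation needs additive replacement and no true interactions, and the documents establish neither.

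**Conclusion.** The point holds in a limited form. The protocol declares a main analysis and then lets the observed outcomes decide whether that model or another is final, for the primary and every secondary outcome. The primary estimate is undetermined until outcomes are fitted, the form of the competing model is open, and no rule covers disagreement between AIC and BIC.

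The likely numerical effect is small. The two models led to different conclusions on significance in about 0.6% of null trials and 2% at RR 0.7. These figures rest on the simulation's assumptions, in particular four strata without centre rather than the 17 × 2 × 2 = 68 cells of the declared factorial, so they show the direction and are not a bound. The 15% and 34 to 45% disagreement figures apply only if continuous length is added as a single term, and the upper range depends on assumed non-centralities.

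The plan should be changed because one sentence contradicts another on which analysis is primary. Nothing here shows an inflated error rate.

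**What to change.** Delete the AIC/BIC selection rule for the primary and the secondary outcomes. Name one model as the single primary analysis; the simplest choice is the already declared analysis adjusted for the randomisation strata. Report the continuous cervical-length model as a named sensitivity analysis that cannot replace it, and state whether the continuous term is added to the two-category factor or replaces it. Use the named model for any interim look at the primary outcome as well.

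Removing the rule does not require abandoning the declared adjustment in favour of main effects with continuous length. That would be a separate choice.

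The cost is one or two sentences in the protocol and the statistical analysis plan, settled before outcomes are analysed by arm. N = 936 and two-sided alpha 0.05 are unchanged. The downside is a possible small loss of precision if the other model fits better; in the simulation at RR 0.7, power was 77.9% for the fixed model against 77.9 to 78.4% after selection, a difference of at most 0.5 percentage points.
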